#### Secondary objectives

To measure implementation challenges, we will investigate accuracy, feasibility, and acceptability, including stigmatization. Accuracy will be measured by comparing intake based on opening of pillboxes with drug intake based on isoniazid urine strips. Feasibility will be measured through practicality, actual fit, utility, and trialability (meaning if it can be tried out on a limited basis before deciding to adopt it permanently). Also, acceptability will be measured through comfort, relative advantage, and credibility. Another aspect of acceptability is also the percentage of patients that actually agree to participate. These feasibility and acceptability outcomes will be measured through information from the evriMED system (number of intakes, number of sent reminders, network failures, battery failures, etc.) and through qualitative interviewing of participants who finished their treatment course. Furthermore, we will measure stigmatization through the Van Rie 2008 Stigma scale specific for TB [51]. This scale consists of several items a participant has to answer on a four-point Likert scale ranging from ‘strongly disagree’ to ‘strongly agree’, such as ‘Some people are afraid of those with TB’ and ‘Some people who have TB feel alone’.

### Sample size calculation and randomization

We calculated that to be able to detect a difference of mean adherence from 79% to 90%, with a power of 80% and significance of 0.05, we would need a sample size of 336 (168 in each arm). As we will use cluster randomization, we used a cluster correlation factor of 0.01. We will need to include 600 patients, 50 in 12 clusters. Considering a drop-out rate of 10%, we anticipate enrolling 660 participants in total. For a period of 8 months, all patients diagnosed with susceptible TB will be asked to participate in our study.

The whole Kilimanjaro Region was divided into 12 clusters based on location in the district, level of health care facility, and number of TB cases in 2017 in each clinic. These clusters were then randomly assigned to provide either standard of care or standard of care and pillbox. A random variable was generated in a dataset containing the clusters. Then, the clusters were sorted using a random variable. The first six clusters were assigned to intervention and the last six to control. Randomization was done using Stata 15.1.

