## Background

Tuberculosis (TB) is among the main communicable diseases causing mortality worldwide, with 10.4 million cases in 2017, of whom 1.7 million died [1]. The World Health Organization (WHO) has set targets in its 2017 ‘END TB Strategy’ for reducing TB deaths by 95% and new cases by 90% by 2035 [2]. However, the END TB Strategy is hampered by the rapidly rising rates of multi-drug-resistant (MDR) TB, with 558,000 cases in 2017 worldwide [1]. Currently, TB treatment is the cornerstone of TB control, but inadequate adherence to treatment is a major factor that leads to treatment failures or development of MDR TB. TB patients have to take four types of pills for 2 months and then two types of pills for another four months; if patients adhere to this regime, they will feel much better within the first two weeks. The number of pills and the six-month duration of therapy causes challenges to TB patients with regard to adherence. Several studies have shown that adherence among TB patients in Sub-Saharan Africa is not reaching adequate levels [3–6]. Specifically, two studies in Tanzania have shown that only 79% of TB patients reached levels of 95% adherence to TB treatment in Kilimanjaro and only 83% reached adequate adherence in Mwanza [7, 8]. Having an estimated TB incidence rate of 269 (range 127–464) per 100,000 population in 2017, Tanzania is among the countries with the highest numbers of TB cases [9]. The estimated mortality rate was 47 (range 21–83) per 100,000 population in 2017 and the proportion of TB cases with MDR TB was 0.9% [9]. Treatment success is not satisfying with rates of 90% in Tanzania in 2017 [9]. The WHO has recommended directly observed treatment (DOT) for many years to improve adherence. However, the implementation of DOT in Sub-Saharan African countries, including Tanzania, is limited, leading to adherence to treatment still being a major challenge [10]. As such, the END TB Strategy recommends to use digital adherence technologies, but with the remark that evidence that such technologies improve adherence is still limited [2].

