### Data management and analyses

In this study, we believe a data monitoring committee is not needed as we are not testing a medicinal product or invasive product or device. We will use an established data management team to control data management and quality. In addition, we will not conduct interim analyses to make decisions on whether to stop the trial.

Data will be collected using electronic data capturing (EDC). We will use tablets in which a simple case report form (CRF) is pre-programmed. Data will be entered in RedCap (Research Electronic Data Capture). REDCap is a secure, web-based application designed to support data capture for research studies, providing 1) an intuitive interface for validated data entry; 2) audit trails for tracking data manipulation and export procedures; 3) automated export procedures for seamless data downloads to common statistical packages; and 4) procedures for importing data from external sources [52]. RedCap will only be accessible by authorized users. The data of participants is coded and will be treated anonymously. Data validation will be conducted using the automated query feature. Statistical tests will be performed at a two-sided significance level of 0.05. Analyses will be performed with Statistical Product and Service Solutions (IBM SPSS Statistics, Chicago, USA).

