#### Primary objective

To answer the primary objective, we will compare adherence measures between the different arms. We will compare the mean adherence levels (percentage of medication taken) between arms and we will also compare percentage of participants that adhered according to the cut-off levels of 99%, 95%, 90%, and 75% (for example, 10% of patients had a mean adherence level of 99% or more). For continuous adherence levels, we will use *t*-tests or nonparametric tests depending on distribution of data. For cut-off levels, we will use χ^2^ tests. To account for the cluster effect in the analysis, we will conduct mixed effects regression models.

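### The sample size is stated for mean adherence rising from 79% to 90%, but its figures are those of a two-proportion calculation, so the 80% power is not established for the mean

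*Protocol article*

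**What the plan says.** All references are to the protocol article.

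- **Sample size calculation and randomization.** The aim is to "detect a difference of mean adherence from 79% to 90%, with a power of 80% and significance of 0.05", and for this "we would need a sample size of 336 (168 in each arm"). For clustering, "we used a cluster correlation factor of 0.01", which leads to 12 clusters of 50, or 600 patients. The paragraph ends: "Considering a drop-out rate of 10%, we anticipate enrolling 660 participants in total". It gives no SD and cites no source for the 79%.
- **Background.** Two Tanzanian studies are cited for current adherence. The Kilimanjaro result is that "only 79% of TB patients reached levels of 95% adherence to TB treatment in Kilimanjaro".
- **Data management and analyses.** "Statistical tests will be performed at a two-sided significance level of 0.05".
- **Primary objective (analysis).** "We will compare the mean adherence levels (percentage of medication taken) between arms". The same sentence adds the percentages of participants at or above 99%, 95%, 90% and 75%. It does not rank these comparisons or say which of them the sample size serves.

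**The concern.** The 79% in the Background is a share of patients: those who passed a 95% threshold. In the sample size paragraph 79% appears as an average of the percentage of medication taken. These are different quantities, and the one cannot stand in for the other. The paragraph cites no source, so the link is an inference, but the figure and the region are the same and no other 79% adherence figure appears in the article.

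Two things are at stake. A reader will attach 80% power to the mean comparison, although no calculation for a mean was shown. A null result on the mean would then be read with more confidence than the plan supports. Also, the target of a mean rising from 79% to 90% may not be reachable on the mean scale, so a result could not sensibly be judged against it.

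**Working it through.** **Inputs.** From the article: 79% and 90%, 80% power, two-sided 0.05, intracluster correlation (ICC) 0.01, 6 clusters per arm, 50 per cluster, drop-out 10%.

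**1. The stated 168 per arm, as two proportions.** The average proportion is 0.845. The variances are 0.79 × 0.21 = 0.1659 and 0.90 × 0.10 = 0.0900, which sum to 0.2559.

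n = [1.96 × √(2 × 0.845 × 0.155) + 0.8416 × √0.2559]² / 0.11² = (1.0031 + 0.4257)² / 0.0121 = **168.7 per arm**.

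The unpooled version gives 166. Power at exactly 168 per arm is 79.8%. The stated figure reproduces.

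**2. The stated clusters and total.** Clusters per arm = 1 + 7.849 × (0.2559/50 + 0.01 × 0.2559) / 0.0121 = **5.98**. That is 6 per arm, 12 clusters and 600 patients. This step also uses the variance of a yes/no outcome.

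**3. The same figures, as a comparison of means.** A mean comparison needs an SD, and none is given. The SD that would return 168 per arm is 11 / (2.80 × √(2/168)) = **36.0 points**. The SD of a 0/1 variable at these proportions is √(0.2559/2) = 35.8 points. The calculation passes as one for means only if adherence behaves like a yes/no variable.

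**4. Is a mean of 79% compatible with the Background?** If 79% of patients have at least 95% adherence, they contribute at least 0.79 × 0.95 = 0.7505 to the mean. For the overall mean to be 0.79, the other 21% can average at most (0.79 − 0.7505) / 0.21 = **0.188**, about 19%. The Background figure alone bounds the mean between about 75% and just under 0.79 + 0.21 × 0.95 = 99%. Adherence cannot exceed 100%, so an 11-point gain is impossible once the control mean is above 89%.

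**5. Power for the proportion, allowing for few clusters.** The design effect is 1 + 49 × 0.01 = 1.49. With 300 per arm the noncentrality is 0.11 / √(0.2559 × 1.49/300) = 3.09. On 10 degrees of freedom (12 clusters less 2) the power is **79.4%**.

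**6. Power on the mean for the equivalent shift (illustration only).** Assume that the share at or above 95% rises from 79% to 90%, that these patients are uniform on 95–100% (mean 97.5%), and that ICC 0.01 also holds for the mean. The remaining patients' mean and SD are assumed, because the article does not give them. The design is that of step 5.

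| Non-adherers: mean | Overall mean moves | Power, SD 0 | Power, SD 10 points |
|---|---|---|---|
| 50% | 87.5% to 92.7% | 79% | 77% |
| 85% | 94.9% to 96.2% | 76% | 53% |

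Power falls further with more spread: with mean 50% and SD 20 points it is 71%.

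**7. Drop-out.** 600 × 1.10 = 660, the stated figure. But 660 × 0.90 = **594**, and 600/0.90 = 666.7, so 667 would be needed to keep 600. With 297 per arm (49.5 per cluster, design effect 1.485) the power for the proportion is **79.1%**.

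**The case against.** Several points can be made for the plan as written.

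- **The difference as worded would be adequately powered.** Adherence lies between 0 and 100%, so if the means really were 79% and 90%, the average SD could not exceed about 36 points. With 12 clusters of 50, ICC 0.01 and 10 degrees of freedom, power for 11 points is about 79% at SD 36, 91% at SD 30 and 98% at SD 25. This stands. A reader might infer from the mislabelled endpoint that the trial is underpowered, and the article does not support that.
- **The true control mean is unknown.** A reader might infer that it must be near 90% already. That follows only from an assumed mean among non-adherers, such as 50–85%. The Background excludes nothing between about 75% and 99%, so 79% is implausible but not ruled out. This stands too.
- **The powered comparison is in the plan.** The 95% cut-off is among the comparisons listed under the primary objective, and the mean is not declared to outrank it. The calculation thus serves a planned comparison under the wrong name. That limits the harm, but the sample size paragraph still names the mean, and nothing ties the power to the 95% cut-off.
- **The drop-out slip is trivial.** It moves power from 79.4% to 79.1%. Agreed; it is worth correcting only because the same paragraph is being edited.

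**Conclusion.** The point holds as a mismatch between the endpoint named and the endpoint calculated. The figures 168, 6 clusters per arm and 600 all follow from a comparison of 79% with 90% as proportions. The stated 80% power belongs to the proportion with at least 95% adherence, one of four listed cut-offs, where 79.4% is obtained on 10 degrees of freedom. It is not established for mean adherence.

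For the mean, the size of the problem cannot be fixed from the article. For the equivalent shift, the illustration runs from about 79% down to about 53% (non-adherer means of 50–85%, SDs of 0–10 points), and lower with more spread. That range rests on assumed inputs and is no estimate of the trial's power. What does follow from the Background figure is that a control mean of 79% would need the remaining fifth of patients to average at most about 19% adherence, which makes an 11-point gain in the mean implausible as a target.

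The conclusion assumes that the 79% in the sample size paragraph is the Background's Kilimanjaro figure. If it came from elsewhere, the missing SD and the match to the two-proportion formula would remain.

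**What to change.** 1. In the sample size section, restate the target as: to detect an increase in the proportion of participants with at least 95% adherence from 79% to 90%.
2. Under the primary objective, name that proportion as the comparison that the sample size serves.
3. Make no power claim for mean adherence unless a justified control mean, SD and target difference are given. Giving these three is the alternative if the investigators want the mean to carry the power statement. Whether the mean is then ranked as primary or secondary is their choice.
4. In the same edit, state the drop-out step as 594 evaluable from 660 enrolled, with power of about 79.1%.

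The cost is wording only; items 1, 2 and 4 need no additional patients. The Trial status section describes recruitment as not yet started, so the change can be made before any outcome data exist.

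### The 10% drop-out allowance is added by multiplication, so 660 enrolled leaves 594, 6 short of the plan's own 600; a minor slip that does not make the trial underpowered

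*Protocol article*

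**What the plan says.** All the relevant figures stand in the Protocol article, almost all of them in the section Sample size calculation and randomization.

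- The trial is sized "to be able to detect a difference of mean adherence from 79% to 90" per cent. No standard deviation is given.
- Before clustering, "with a power of 80% and significance of 0.05, we would need a sample size of 336 (168 in each arm").
- For clustering, "we used a cluster correlation factor of 0.01".
- The resulting need is put as "We will need to include 600 patients, 50 in 12 clusters".
- The drop-out allowance follows in the next sentence: "Considering a drop-out rate of 10%, we anticipate enrolling 660 participants in total".
- On allocation: "The first six clusters were assigned to intervention and the last six to control".

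The section Data management and analyses adds: "Statistical tests will be performed at a two-sided significance level of 0.05".

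The order of the sentences fixes the roles of the two totals. The 600 comes before the drop-out allowance and the 660 after it.

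**The concern.** If 600 patients are needed after losses and 10% of those enrolled are expected to be lost, the enrolment target should be the number that leaves 600 when a tenth is taken away. The article instead adds a tenth of 600 to 600. The two operations differ, and the second always gives too few.

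Three printed figures (600, 10% and 660) therefore cannot all hold together. This is not a detail that a condensed article has left to a fuller document. The enrolment target is an operational figure, used for planning recruitment and later for reporting whether the trial reached its size, so it should agree with the requirement beside it.

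**Working it through.** **Inputs from the article.** Need 600 in 12 clusters of 50; drop-out 10%; enrolment 660; 79% versus 90%; two-sided 0.05; 80% power; 168 per arm unclustered; intracluster correlation 0.01; six clusters per arm.

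**1. Reproduce the stated enrolment.**
600 × (1 + 0.10) = 660. This matches exactly, so the method was multiplication.

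**2. What 660 delivers at 10% drop-out.**
660 × (1 − 0.10) = 594.
594 / 12 = 49.5 per cluster on average.
Shortfall: 600 − 594 = 6.

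**3. What drop-out 660 can bear while keeping 600.**
(660 − 600) / 660 = 60/660 = 9.1%.

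**4. Enrolment that keeps 600 at 10% drop-out.**
600 / (1 − 0.10) = 666.7, so 667.
Difference from 660: 7 patients; 7/667 = 1.0%.

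**5. Does the shortfall matter against the plan's other inputs?**
Design effect at 50 per cluster: 1 + (50 − 1) × 0.01 = 1.49.
336 × 1.49 = 500.6, so about 501.
The 594 retained exceeds this by about 93.

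**6. Effect on power.** This step needs an assumption: 79% and 90% are treated as proportions, because no standard deviation is given for mean adherence. On that basis the usual two-proportion formula gives 169 per arm (pooled variance) or 166 (unpooled), which roughly reproduces the stated 168.

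Effective number per arm:
- at 600: 300 / 1.49 = 201.3
- at 594: 297 / [1 + (49.5 − 1) × 0.01] = 297 / 1.485 = 200.0

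The normal approximation is Φ[(0.11 − 1.96 × SE0) / SE1], where SE0 is the pooled and SE1 the unpooled standard error. The t version uses a noncentral t on 10 degrees of freedom (12 clusters less 2) with the unpooled standard error.

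| Reference distribution | 600 evaluable | 594 evaluable | Loss (points) |
|---|---|---|---|
| Normal approximation | 86.5% | 86.3% | 0.2 |
| t on 10 degrees of freedom | 79.4% | 79.1% | 0.3 |

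Steps 1 to 5 do not depend on the assumption in step 6.

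**The case against.** The strongest reply is that this is too small to raise. The gap is 6 evaluable patients, and the 10% is itself a round planning figure. The article also describes recruitment by period: all eligible diagnoses over 8 months are to be approached, and 660 is what the authors anticipate rather than a count at which enrolment stops. Seven patients lie well inside the uncertainty of such a forecast. All of this stands, and it limits the point to a correction of wording. It does not make 660 agree with 600 and 10%.

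A second reply is that the need of 600 is already generous on the plan's own inputs. This also stands. The 600 implies a design effect of 600/336 = 1.79, against 1.49 from the stated correlation. Where 600 comes from is a separate question, but 594 is clearly enough for what the stated correlation requires.

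A reader might go further and infer that a trial with 12 clusters has no slack, so that the slip takes power below 80%. The documents do not support that. It depends on a t reference with 10 degrees of freedom, whereas the analysis section names t-tests or nonparametric tests, χ² tests and mixed effects regression without any degrees-of-freedom rule. Even on that reference, power is already 79.4% at the full 600, and enrolling 667 would only return it to that value. The drop-out allowance is not what decides it. On the normal approximation, power is about 86% either way.

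A reader might also round up to 56 per cluster, 56 × 12 = 672. That presumes equal enrolment in whole patients in every cluster. The article gives 50 per cluster for the need, but it forms clusters partly by the number of TB cases and does not require equal enrolment. Only 667 follows from the text.

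**Conclusion.** The point holds as a minor arithmetic correction. The stated enrolment of 660 does not deliver the stated 600 at the stated 10% drop-out: it leaves 594, or it covers 9.1%. The correct inflation is 667.

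The consequence is about 1% of enrolment and 0.2 to 0.3 points of power, the latter on the assumption that 79% and 90% can be treated as proportions with an intracluster correlation of 0.01. The slip is no ground for calling the trial underpowered.

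**What to change.** Change one sentence in Sample size calculation and randomization, in either of two ways.

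- Keep 660, and state that it allows for about 9% drop-out or that it leaves 594 evaluable at 10%. This needs no further patients.
- Keep the 10%, and restate the enrolment target as 667, showing 600/0.90. This adds 7 patients. Should equal enrolment in every cluster be intended, say so and give the per-cluster number.

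The Trial status section says that recruitment had not started, so either change was open when the article was written. Neither alters the design or the analysis.

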#### Baseline characteristics

Baseline characteristics data will be summarized for all participants and for the two arms. The characteristics information includes patient identification number, place of living/work, contact phone number, sex, age, referral option, phone number of treatment supporter, name of health facility, DOT option (health facility DOT or home-based DOT), and HIV status, including co-medication. We shall also take sputum smear and isoniazid urine tests for measuring treatment outcomes.

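### Twelve clusters were split 6:6 by an unrestricted sort, and the stated analyses give no role to the cluster factors or baseline covariates; fix an adjusted primary model before outcome data are seen

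*Protocol article*

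**What the plan says.** All references are to the protocol article.

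- **Forming the clusters** (Sample size calculation and randomization): the article describes Kilimanjaro as "divided into 12 clusters based on location in the district, level of health care facility, and number of TB cases in 2017 in each clinic".
- **Allocating them** (same section): "Then, the clusters were sorted using a random variable", and "The first six clusters were assigned to intervention and the last six to control". No strata, pairs or balance constraint are described.
- **Timing**: that section reports randomisation as already done, while Trial status says recruitment has not started.
- **Baseline data** (Baseline characteristics): these are to be summarised overall and by arm. They include sex, age, name of health facility, and "DOT option (health facility DOT or home-based DOT), and HIV status, including co-medication".
- **Analysis** (Primary objective, under Data management and analyses): t-tests or nonparametric tests for mean adherence, chi-square tests for the cut-offs, and then "To account for the cluster effect in the analysis, we will conduct mixed effects regression models". No fixed covariate is named and none is ruled out.

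**The concern.** Three cluster-level characteristics were known before the draw and were thought important enough to define the clusters, yet they were not used to balance the arms. With only 12 units, an unrestricted split often leaves the arms with different facility mixes. The Background itself lists patient characteristics and the organisation of services among the influences on adherence, so such differences may matter for the outcome.

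A second route is at patient level. Patients are approached after their clinic's arm is fixed, the intervention is a visible pillbox, and no masking of recruiters or patients is described. Eligibility requires willingness to use the device, and the Background and Discussion expect the device to be stigmatising. If willingness to join differs between arms, the patient mix can differ too, and a random cluster effect does not remove that.

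At stake are the precision of the main comparison and how convincing it is if the arms turn out visibly unequal.

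**Working it through.** **1. The plan's own figure.** The inputs are 79% versus 90%, two-sided 0.05 and 80% power. The article gives no standard deviation, so I treated the outcome as binary:

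n per arm = [1.96·√(2·0.845·0.155) + 0.842·√(0.79·0.21 + 0.90·0.10)]² / 0.11² = 168.7

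That is 169 per arm or 338 in total, against the stated 336 (168 per arm). The figure reproduces to within rounding, which supports using binary variances below.

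**2. How often the draw is uneven.** There are C(12,6) = 924 possible 6:6 allocations. The article does not say how many clusters share a facility level, so I assume that 4 of 12 do.

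| Split of the 4 clusters | Allocations | Probability |
|---|---|---|
| 2:2 | 420 | 45.5% |
| 3:1, either way | 2 × 224 = 448 | 48.5% |
| 4:0, either way | 2 × 28 = 56 | 6.1% |

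A 3:1 or worse split therefore has probability 504/924 = 54.5%. If the factor were present in 6 of 12 clusters, 4:2 or worse would have probability 56.7% and 5:1 or worse 8.0%.

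**3. Shift in an unadjusted difference, given the split.** Shift = gap × (difference in cluster counts)/6. The gap in adherence between cluster types is not in the article, so a range is shown.

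| Assumed gap | 3:1 split (gap × 2/6) | 4:0 split (gap × 4/6) |
|---|---|---|
| 2 points | 0.7 | 1.3 |
| 4 points | 1.3 | 2.7 |
| 8 points | 2.7 | 5.3 |

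The target difference is 11 points, so a 3:1 split moves the estimate by 6% to 24% of it (0.67/11 to 2.67/11).

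**4. Precision at stake.** With the stated ICC of 0.01 and 50 per cluster, the design effect is 1 + 49 × 0.01 = 1.49. The between-cluster share of the variance of the arm difference is 50 × 0.01/1.49 = 33.6%. With 300 per arm:

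SE = √[(0.1659 + 0.09) × 1.49/300] = 3.57 points

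Power for 11 points (noncentral t):

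- No cluster-level term, 10 df: 79.4%.
- One term that explains nothing, 9 df: 78.4%.
- One term that explains all between-cluster variance (0.99 replaces 1.49, SE 2.91 points), 9 df: 91.9%.

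The two 9-df figures bound what one cluster-level term can do to power at this ICC: a loss of about 1 point at worst and a gain of about 12 points at best.

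**5. DOT option.** Study area says patients choose their DOT type, and 2574 of 2681 (96%) chose home-based. At that rate about 24 of 600 participants would differ (600 × 107/2681). Clusters were allocated before recruitment, so the choice follows allocation and could be affected by it.

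**The case against.** The strongest reply is that nothing in the article says the model will be unadjusted. It names the class of model and is silent on fixed effects, and an article commonly leaves a covariate list to the analysis plan. That stands: a reader might infer that the authors decided against adjustment, but the documents do not support it, and a missing list alone would not be a finding.

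A reader might also infer that chance imbalance biases the trial or confounds its estimate. That does not hold either. Over all 924 allocations the shifts cancel, and a random cluster effect carries that variation into the standard error, provided small-sample inference is used. The shifts in the working are conditional on a particular split and on an unadjusted model. An unrestricted draw is a valid design.

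Two further points stand. The 4-of-12 and 2-to-8-point inputs are illustrative. The article is also unclear on cluster make-up: the three factors may have been used to make clusters alike, and a cluster may mix facility levels. Nor is there evidence here that the ICC of 0.01 is too small. At the variance for 79%, an 8-point gap would contribute 0.08² × (1/3)(2/3)/0.1659 = 0.0086, which fits within it.

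The reply does not reach recruitment after allocation. Differential consent is not averaged out by randomising clusters, and the only purpose stated for the mixed model is clustering.

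**Conclusion.** The point holds as one of precision, of accuracy given the allocation actually drawn, and of partial protection against differences in patient mix. It does not show an invalid primary analysis.

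The allocation method is documented and can no longer be changed. If 4 of 12 clusters share a prognostic feature, an uneven split is more likely than not (54.5%). A 3:1 split would shift an unadjusted difference by 0.7 to 2.7 points out of 11 for gaps of 2 to 8 points. At the stated ICC about a third of the variance of the comparison lies between clusters, and a good cluster-level covariate could recover part of it. The size of any recruitment effect cannot be derived from the article.

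The change is worth making because it is cheap, uses data already to be collected, and is credible only if fixed in advance.

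**What to change.** Before any outcome data are seen, state that the primary mixed model contains, besides arm and the random cluster effect:

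- one cluster-level term: facility level, or 2017 caseload if clusters mix facility levels;
- age, sex and HIV status at patient level;
- inference on small-sample degrees of freedom based on the number of clusters.

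Report the model without covariates as a sensitivity analysis. Do not adjust for DOT option: it is chosen after allocation, so adjusting could introduce bias, and with 96% in one category there is little to gain. Keep to one cluster-level term, since 12 clusters support few.

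The cost is a change of wording and one cluster-level degree of freedom. The critical t value rises from 2.23 on 10 df to 2.26 on 9, and power falls from 79.4% to 78.4% if the term explains nothing. Age, sex, HIV status and facility name are already on the baseline list, facility level should be derivable from the name, and 2017 caseload was used to form the clusters. Adjustment for measured patient characteristics is only a partial remedy for differential recruitment.
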